## RESEARCH PROPOSAL FOR THE WELLCOME TRUST MASTERS FELLOWSHIP

### Research Question:

What is the effectiveness of Telemedicine in identifying cases of Diabetic Retinopathy (DR) attending diabetes clinics compared with a universal hospital referral strategy?

### Rationale

Diabetes Mellitus (DM) is a major health problem estimated to have affected 171 million people worldwide in 2000 and projected to rise to 366 million in 2030 [1]. India has the highest number of people with diabetes in the world with 31.7 million in 2000. This figure is estimated to rise to 79.4 million by 2030, based only on demographic changes, i.e. the growth of the older population where diabetes is more prevalent. However, lifestyle changes, especially increasing levels of obesity may lead to an even greater number of people with DM in India. Consequences of DM include Diabetic Retinopathy (DR) which is a major cause of avoidable blindness in both developing and the developed countries [2] and patients with DR are 25 times more likely to become blind than non-diabetics. Various studies conducted in India shows that 12 – 18% of the diabetic population develops DR [3-6]. In a population-based study conducted by Aravind Eye Hospitals in the Theni district of south India the prevalence of DM was found in 10.8 % of people aged 30 and over; of whom 12.2% had DR [4]. Prevalence rates of both DM and DR were higher in older people and in urban compared to rural areas.

Timely treatment can prevent vision loss due to diabetic retinopathy [7]. Treatment can yield substantial cost savings compared with the direct costs for those disabled by vision loss [8]. Though all diabetics require regular monitoring for diabetic retinopathy, only a very small proportion of the “known diabetics” receive a comprehensive eye examination [8]. Factors such as lack of access to eye hospitals, lack of ophthalmologists trained in diabetic retinopathy management and lack of awareness both by diabetic physicians, optometrists and patients. In particular, lack of knowledge among physicians and optometrists regarding diabetic retinopathy is highly unacceptable [9]. A study conducted on the awareness level of physicians in India reported that more than 67% of the physicians were unaware and about 10% were only partially aware of diabetic retinopathy [10]. When patients do attend ophthalmology clinics, it may be at a late stage of disease and their prognosis is poor. Treatment of end stage DR does not provide satisfactory results and is frustrating for both the patient and the ophthalmologist [3].

Population screening for diabetes and DR is costly and therefore is not appropriate as a regular screening strategy to identify DR. In the exiting context of healthcare, the critical challenges that need to be addressed include:

- a. Identifying diabetics at risk of DR through targeted screening of known diabetic patients at diabetic/physician centres
- b. Ensuring easy access to an ophthalmic centre for the diabetic patients who require further intervention
- c. Enabling patients diagnosed with DR to comply with regular follow-up either at diabetic/physician centres or the ophthalmic centres, as appropriate

The conventional system is to refer all patients identified with diabetes to undergo an eye examination at an ophthalmic centre. However, only a very small percentage of the people referred in this mode actually present at the ophthalmic centre for an eye examination to confirm or rule out the presence of DR [11,12]. Thus opportunities for intervention and management of DR are lost.

Fundus examination is adequate for diagnosing DR and its severity. Technological advances in ophthalmic care have enabled the availability of digital imaging of fundus making it easier and more widely accessible [13]. Digital retinal photography without mydriasis by trained office staff has been reported as an effective mechanism to examine patients who are in need of diabetic retinopathy screening [14]. Use of telemedicine has been, in many instances, found to be valid and effective in achieving better outcome in the screening of, and interventions for, diabetes related complications as well as other systemic diseases [15-18]. Implementing retinal imaging technology in a primary care setting has been found to have resulted in a significant increase in rate of DR surveillance and in the rate of laser treatment for DR [11, 19]. But, there has not been an RCT to evaluate robustly the effectiveness of telemedicine in case finding of DR.

Coupling the recent advances in ophthalmology and information technology, Aravind Eye Hospitals has developed an innovative opportunistic case finding approach involving diabetes centres that binds digital retinal imaging with a robust IT solution - basically aimed at creating access for retinal screening. Telemedicine based digital retinal imaging for diabetic retinopathy has been installed in diabetes centres and the fundus images of suspected patients are sent to the Reading & Grading Centre at Aravind Eye Hospital where the images are graded using an indigenously developed software ADRES 4.0 (Aravind Diabetic Retinopathy Evaluation Software) and a report is sent back to the diabetes centre [20].

However, up-scaling this approach in India and other developing countries requires evidence about its effectiveness of achieving the desired objective. The proposed study in diabetes centres compares the effectiveness of telemedicine-based screening and hospital referral with that of a universal hospital referral strategy i.e. referring all eligible diabetic patients.

**Objective:** To compare the effectiveness of identifying Diabetic Retinopathy through referral followed by telemedicine based digital retinal imaging in Diabetes Centres with that of the a universal referral system

**Hypothesis:** Telemedicine based digital retinal imaging in a diabetes centre will identify proportionately more diabetic patients with DR and be associated with higher acceptance rates compared to Universal referral.

### **Study Plan:**

**Design:** The design is a cluster randomised trial (RCT). Diabetes centres will be randomized to one of two strategies: telemedicine referral (TR) or universal referral (UR). Patients attending diabetes centres within a distance of 10 kms from Aravind Eye Hospital Madurai (i.e. within the urban and peri-urban area) will undergo one of these randomized interventions. A cluster RCT is required to avoid patients in the same centre being offered different screening interventions which might present both logistic and ethical difficulties.

**Procedures:** All patients identified in either arm meeting the inclusion and exclusion criteria will be referred to the clinic study coordinator who will seek fully informed patient consent (see below, under Ethical considerations) prior to enrolling the patient. Those enrolled will be counselled about DM and the importance of vision screening, and will be invited for either digital fundus imaging at the diabetes centre (TR) or for detailed examination for diabetic retinopathy (DR) at an eye hospital (Aravind Eye Hospital Madurai, AEH). Randomisation is at the level of the centre and there is no individual patient randomisation. In TR the diabetes centre will be equipped with a digital imaging system for screening the fundus and the patients diagnosed with DR or probable DR will be counselled to visit AEH for a full retinal examination to confirm (or not) the presence of

DR. In UR, the eligible patients will be counselled and referred to undergo eye examination at AEH. In both the arms the counselling and the awareness creation materials will be standardised.

A total of eight diabetes centres will be identified and four each will be randomly allocated to each arm stratified by distance from Aravind Eye Hospital Madurai. The aim of stratification is to ensure that there is no imbalance in the randomized arms in proximity to the hospital. The stratification criteria will be <5km, ≥ 5-10km. This covers the most densely populated areas (less than 5km), and the outer peri-urban/rural areas. An interviewer cum counsellor will be appointed at each of the diabetes centres in UR who will administer the consent form, collect patient data and do the referral. In the diabetes centres in TR, the interviewer cum counsellor will also be trained in fundus photography through a structured two-weeks training. The study will be carried out for a period of six months and a window of one month after referral will be given for the patient to visit the eye hospital.

At the end of the one month window after the last referral, those patients who have not complied with the referral will be contacted. A short semi structured interview will be conducted with (i) all those who decline referral and/or imaging to understand the barriers to compliance (ii) a sample of those who do attend Aravind Eye Hospital to understand the drivers of acceptance. The topic guide for the interviews will be developed from previous literature and other studies on barriers and drivers to cataract surgery uptake undertaken by Aravind Eye Hospital [21]. The results from these interviews will form a part of the final overall evaluation of the trial by adding a qualitative component. The interviewer will also ask about any other eye examinations that have been conducted by other eye professionals (ophthalmologists or optometrists) since patients may have chosen to attend elsewhere for the eye examination. In this situation information will be sought on the DR findings.

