#### **Diabetic Retinopathy:**

DR will be graded using the standard classification (from reference [8])

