#### **DIABETIC RETINOPATHY DISEASE SEVERITY SCALE**

| Disease Severity Level | Findings Observable upon Dilated Ophthalmoscopy                                                                                                                                                                                                     |
|-------------------------------|------------------------------------------------------------------------------------------------------------------------------------------------------------------------------------------------------------------------------------------------------------|
| No apparent retinopathy       | No abnormalities                                                                                                                                                                                                                                           |
| Mild NPDR                     | Microaneurysms only                                                                                                                                                                                                                                        |
| Moderate NPDR                 | More than just microaneurysms but less than severe NPDR                                                                                                                                                                                                    |
| Severe NPDR                   | Any of the following (4-2-1 rule) and no signs of proliferative retinopathy:
Severe intraretinal hemorrhages and microaneurysms in each of four quadrants
Definite venous beading in two or more quadrants
Moderate IRMA in one or more quadrants |
| PDR                           | One or both of the following:
Neovascularization
Vitreous/preretinal hemorrhage                                                                                                                                                                      |

IRMA = intraretinal microvascular abnormalities; NPDR = nonproliferative diabetic retinopathy;

PDR = proliferative diabetic retinopathy

**Data collection:** A database will be designed to capture:

1. Basic details from the eligible patients such as name, age, contact information, blood sugar level, HBA1C, duration of diabetes, date of diagnoses, other vascular complications etc.

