### *Outcomes*

The primary outcome will be diabetic retinopathy (DR) confirmed by dilated fundus examination at the hospital.

The secondary outcome will be hospital attendance.

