### *Strategies of analysis*

We will report two strategies of analysis for the primary outcome.

The primary intention to treat (ITT) analysis will include all patients eligible for referral in each randomised arm irrespective of compliance with referral. Eligibility for referral is defined according to the protocol, i.e. those who were offered a hospital referral. In the UR arm all patients will be offered a hospital referral. In the TR arm only those identified by teleretinal imaging as requiring further investigation or with inadequate images will be referred.

The secondary per-protocol (PP) analysis will include only patients who complied with referral (defined as attendance at Aravind Eye Hospital or at other eye specialist).

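### The protocol provides no masking of the hospital examiner to arm or image result, although that examination decides the primary outcome and only telemedicine patients come to it with a prior retinal reading

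*Protocol*

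**What the plan says.** The Outcomes section, repeated in the statistical plan at the end of the document, defines a single primary endpoint: "The primary outcome will be diabetic retinopathy (DR) confirmed by dilated fundus examination at the hospital".

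The two arms reach that examination by different routes, set out under Study Plan, Procedures:

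- **TR:** patients whose images are called DR or probable DR are "counselled to visit AEH for a full retinal examination to confirm (or not) the presence of" DR. Strategies of analysis adds a second group, since "only those identified by teleretinal imaging as requiring further investigation or with inadequate images will be referred".
- **UR:** "In UR, the eligible patients will be counselled and referred to undergo eye examination at AEH". No retinal reading comes before this referral.

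On where images are read, the Rationale says they are "sent to the Reading & Grading Centre at Aravind Eye Hospital where the images are graded", with a report returned to the diabetes centre. That text describes the existing programme; Procedures does not say who grades the trial images.

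One severity scale applies to both arms. Its lowest positive grade, mild NPDR, is defined as "Microaneurysms only", and Outcomes sets no higher threshold for a case.

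The protocol does not mention masking of the examiner, independent or duplicate reading, or withholding of the arm or the image report.

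**The concern.** The endpoint is one examiner's judgement. In TR that judgement can follow a report that a lesion has been seen; in UR it never does. Whether one or two microaneurysms are present is the call most easily moved by such a report, and it is enough to make a patient a case.

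If expectation leads to extra positive calls in TR and not in UR, the TR numerator is inflated in the direction of the trial's hypothesis. The inflation enters both the intention-to-treat and the per-protocol results. Cluster randomisation, survey-based standard errors and covariate adjustment do not touch it, because the error lies in how the outcome is measured.

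This is a matter of trial conduct and belongs in Procedures and Outcomes. A separate analysis plan would not be expected to supply it. Cluster allocation makes it hard to mask centres and patients, but it does not prevent masking of an examiner further down the pathway.

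**Working it through.** The protocol gives no figure on masking or on the size of any bias, so there is nothing of its own to reproduce. The calculations below are illustrations on assumed inputs.

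**Illustration 1: over-calling among image-positive patients without DR**

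Inputs:

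- Sensitivity Se = 0.85 and specificity Sp = 0.90 (assumed).
- Over-calling f = 0.05, 0.10 or 0.20: the share of DR-free, image-positive attenders recorded as mild NPDR because of the image (assumed).
- Prevalence p = 0.12 and 0.18, the ends of the range for Indian diabetics in the Rationale. Also p = 0.30, the planning rate for DR diagnosed among referred UR patients in Sample size estimates, used here as a prevalence. If not all referred patients attend, that rate implies a prevalence above 30%, and the inflation is smaller still.

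Formulas: true positives TP = p × Se; false positives FP = (1 − p) × (1 − Sp); DR-free share of image-positives = FP / (TP + FP). The factor on the TR rate, and so on the risk ratio, is 1 + f × FP / TP. It does not depend on the denominator, provided attendance among image-positives is unrelated to true DR status.

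| p | TP | FP | DR-free share | f = 0.05 | f = 0.10 | f = 0.20 |
|---|---|---|---|---|---|---|
| 0.12 | 0.102 | 0.088 | 46.3% | +4.3% | +8.6% | +17.3% |
| 0.18 | 0.153 | 0.082 | 34.9% | +2.7% | +5.4% | +10.7% |
| 0.30 | 0.255 | 0.070 | 21.5% | +1.4% | +2.7% | +5.5% |

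For example, at p = 0.18 and f = 0.10: 1 + 0.10 × 0.082 / 0.153 = 1.054.

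Patients referred for inadequate images are left out. They carry no positive reading, so any DR found among them dilutes these percentages.

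**Illustration 2: the protocol's planning rates**

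Let a be attendance in TR and f the over-calling rate among all TR attenders without DR (both assumed). Observed TR rate = true rate + (a − true rate) × f.

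- Planned rates, 50% v 30% (true risk ratio 0.50 / 0.30 = 1.67). With a = 0.8 and f = 0.10: 0.50 + 0.30 × 0.10 = 0.53, and 0.53 / 0.30 = 1.77. Over a = 0.6 to 1.0 and f = 0.02 to 0.20, the risk ratio runs from 1.67 to 2.00.
- No true difference, 30% v 30%. With a = 0.8 and f = 0.10: 0.30 + 0.50 × 0.10 = 0.35, and 0.35 / 0.30 = 1.17. Over the same ranges it runs from 1.02 to 1.47.

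Both illustrations assume no over-calling in UR.

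**The case against.** The strongest reply is that silence is not evidence of unmasked assessment. A reader might infer that examiners are known to be unmasked, or that they know arm and image result for every TR patient. The documents support neither. The only routing they describe sends the report to the diabetes centre, and patients with inadequate images have no positive reading to be influenced by. Nor do the documents show that image graders and examiners are the same people: the Rationale describes an existing service.

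The wording about confirming is also weaker evidence than it looks. It says confirm or not, the Rationale describes the conventional referral examination in similar terms, and Outcomes applies the same word to both arms.

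On size, all the decisive inputs are assumed. The protocol says DR is more common in urban areas and in older people, which is the population recruited, so the 12% row probably overstates the effect. The direction is not certain either: UR patients are also sent specifically for a DR examination, and an image report may help an examiner find a lesion that is really there.

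All of this stands and limits the claim. It does not remove the asymmetry. TR patients are counselled because of their image result and can pass it on, and nothing written keeps the report from the examiner. The shared scale standardises the criteria but does not mask the person applying them.

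**Conclusion.** The point holds as a gap in the protocol: the examination that decides the sole primary outcome has no stated protection against knowledge of arm or image result, and the two arms differ in what is known beforehand. With microaneurysms alone counting as a case, the outcome is open to expectation bias, most plausibly towards TR.

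The documents cannot show that such bias would occur, or how large it would be. On the assumptions in Illustration 1, the risk ratio rises by about 1% to 5% at 30% prevalence, 3% to 11% at 18% and 4% to 17% at 12%. Against the planned risk ratio of 1.67 this is modest, and over-calling of this size would not by itself produce the planned contrast. It matters more if the true difference is small. The change should be made because it is cheap and the analysis cannot repair the problem afterwards.

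**What to change.** Add to Procedures and Outcomes:

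1. Patients in both arms present at AEH with an identical study referral slip that shows neither arm nor image result.
2. The examiner records the DR grade for each eye before any image report is consulted. The report is then released for clinical use.
3. Where existing staffing allows, the person who graded a patient's image does not examine that patient.

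The cost is one common slip and a rule on the order of recording. The first two items need no extra reader, procedure or sample; the third is conditional so that it does not force new staffing. There are two drawbacks: the examiner sees the report slightly later, and masking stays partial because counselled TR patients may disclose why they were referred.

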### *Statistical analysis*

The data will be analysed using Stata14 (StataCorp Texas). All analyses will take account of the cluster trial design, i.e. the clinic/centre is the unit of randomization. The survey suite of commands ("svy") in Stata will be used for all regression models and cross tabulations.

We will first compare the distribution of characteristics between the trial arms including important prognostic covariates such as age, sex, duration of diabetes. The primary outcome will be analysed using Poisson regression comparing the proportion of DR in the TR arm with that in UR and report the risk ratio (RR) and 95% Confidence Interval (CI) in unadjusted analysis and covariate adjusted analysis. These analyses will be undertaken for the ITT and PP populations. The ITT primary outcome analysis will represent the trial main result.

For the secondary outcome we will investigate characteristics associated with hospital attendance using Poisson regression in a model including randomised arm. We will first check whether characteristics of attendance vary by randomised arm in separate analyses before combining in a single model.

We will also report descriptive analyses based on the semi structured interviews. These will be transcribed into a data base and text analysis techniques will be used to group the responses (this may necessitate translation into English if Tamil software is not available).

**Ethical consideration:** The protocol including the procedures for fully informed consent will be presented for approval from the Research Committee and the Institutional Review Board of Aravind Eye Hospital, India. Eligible participants in the telemedicine arm will be given an information sheet in the local language which will explain the purpose of the study and what

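### Centres are randomised within distance bands, but the analysis does not say that the band enters the primary model, nor which ITT risk ratio is the main result

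*Protocol*

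**What the plan says.** **Design.** Protocol, Study Plan: eight centres, of which "four each will be randomly allocated to each arm stratified by distance from Aravind Eye Hospital Madurai". The bands are given as "The stratification criteria will be <5km, ≥ 5-10km", and the purpose as "The aim of stratification is to ensure that there is no imbalance in the randomized arms in proximity to the hospital". The number of centres in each band is not stated.

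**Outcome and population.** Under Outcomes, the primary outcome is retinopathy confirmed by a dilated examination at the hospital. Under Strategies of analysis, the ITT set keeps referred patients whether or not they attend.

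**Analysis.** Protocol, Statistical analysis: "All analyses will take account of the cluster trial design, i.e. the clinic/centre is the unit of randomization". Stata's svy commands are to be used for every regression model. For the primary outcome, a Poisson model will "report the risk ratio (RR) and 95% Confidence Interval (CI) in unadjusted analysis and covariate adjusted analysis". The ITT analysis is named as the main result, which ranks it above per-protocol. Nothing ranks the unadjusted against the adjusted ratio.

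**Covariates.** No adjustment set is listed. The examples, "important prognostic covariates such as age, sex, duration of diabetes", describe the baseline comparison of the arms. Distance appears under Data checking as a variable to be categorised, but it is not linked to the randomisation bands or to the primary model.

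The Statistical Plan at the end of the document repeats the analysis text and is equally silent on the band.

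**The concern.** A patient with retinopathy who never reaches the hospital cannot be a hospital-confirmed case. Anything that affects the journey can therefore affect the primary outcome, and the design already singles out proximity for balancing. Stratified allocation makes the two arms alike on the band. An analysis that omits the band does not credit that balance: the near-far difference is counted as noise between centres.

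With only eight centres, this term can matter a great deal or not at all, depending on how strongly distance predicts the outcome. At stake are the width of the main interval and whether its stated 95% can be trusted. A second weakness does not depend on distance: with two ITT ratios, no covariate list and no ranking, the headline figure could be chosen after the results are seen.

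**Working it through.** **Inputs from the Protocol.** Sample size estimates: 616 patients, equal arms, 30% against 50%, design effect 2. Study Plan: eight centres, four per arm. Hence 616/8 = 77 per centre and a mean rate of 40%.

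The total of 616 is taken as given. The stated inputs (two-sided 0.01, 90% power) give 177 per arm × 2 (design effect) × 2 arms = 708. A one-sided 0.01 gives 154 × 2 × 2 = 616. That is a separate matter.

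**Assumed, not in the Protocol.** Four centres per band, two per arm in each; equal centre sizes; and the share f of between-centre variance due to the band, run from 0 to 100%. I work with differences between centre proportions.

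**Step 1: variance of centre means.**
- ICC = (2 − 1)/(77 − 1) = 0.0132
- Between-centre variance B = 0.0132 × 0.40 × 0.60 = 0.00316
- Sampling variance W = 0.24 × (1 − 0.0132)/77 = 0.00308
- A share f corresponds to a near-far gap of 2√(fB). The largest gap that design effect 2 allows is 2√0.00316 = 0.112, or 11.2 points.

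**Step 2: centre-level interval with and without the band.** Let v = B(1 − f) + W.
- With the band: SE = √(v/2), 5 df, critical value 2.571
- Without it: SE = √((v + 4fB/3)/2), 6 df, critical value 2.447

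| Share f | Gap (points) | SE without | SE with | Interval ratio, with/without |
|---|---|---|---|---|
| 0% | 0 | 0.0558 | 0.0558 | 1.05 |
| 15% | 4.4 | 0.0565 | 0.0537 | 1.00 |
| 25% | 5.6 | 0.0570 | 0.0522 | 0.96 |
| 50% | 7.9 | 0.0581 | 0.0482 | 0.87 |
| 100% | 11.2 | 0.0604 | 0.0392 | 0.68 |

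Mean widths over 100,000 simulated trials agree: 0.2734/0.2623 = 1.04 at 0%, 0.2552/0.2680 = 0.95 at 25%, 0.2360/0.2742 = 0.86 at 50% and 0.1921/0.2870 = 0.67 at 100%. Break-even is about 14-15% with 5 against 6 df, and about 10% if 6 against 7 df are used.

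**Step 3: error rate and power of the centre-level t analysis (same simulation).**

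| Share f | Type I error at nominal 5%, without / with | Power at two-sided 0.01, without / with |
|---|---|---|
| 0% | 4.9% / 5.0% | 52% / 46% |
| 25% | 3.7% / 5.0% | 50% / 52% |
| 50% | 2.4% / 5.0% | 48% / 60% |
| 100% | 0.5% / 5.1% | 41% / 80% |

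The low powers reflect critical values of 3.707 (6 df) and 4.032 (5 df) at the 1% level.

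**Step 4: the method actually planned.** With four equal centres per arm, the svy linearised variance is (8/7) × SS/16, where SS is the residual sum of squares of the centre means, referred to t on 7 df (2.365).
- Arm only, no distance effect: SS has 6 df, so the expected variance is (8/7)(6/16)v = 0.429v against a true 0.5v. The SE ratio is √0.857 = 0.926. The effective critical value is 2.365 × 0.926 = 2.19, and the two-sided tail of t on 6 df is 7.1%.
- Arm only, simulated: 7.1%, 6.0%, 5.4% and 3.6% at shares of 0, 15, 25 and 50%, and about 1% at 100%.
- Band added to the svy model: SS has 5 df, so the variance is 0.357v and the SE ratio √0.714 = 0.845. The effective critical value is 2.00, and the tail of t on 5 df is about 10%.
- Band only declared as an svy stratum: within a band, the two arms' deviations enter the arm contrast with opposite signs and average to zero. Centring within bands therefore does not remove the near-far difference.

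**The case against.** **Silence is not exclusion.** A reader might infer that the plan leaves the band out. The text does not say that. The covariate set is open, distance is a prepared variable, svy can declare strata, and a separate SAP might settle it. This stands, so the point is that the plan does not state the band's role. It still merits raising: the text spells out which design feature the analysis respects and names the centre only, one of the two headline ratios is unadjusted by definition, and the appended Statistical Plan repeats the gap.

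**The loss of precision is conditional.** The Protocol gives no effect of distance on attendance or on retinopathy, and states only that balance is the aim. The band describes the centre, whereas patients may live up to 25 km from the hospital (Exclusion criteria), so it is only a proxy for travel. This stands. Below a share of roughly 10-15%, including the band widens the interval.

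**A reader might assume very large gains.** A 15-point near-far gap exceeds the 11.2 points that design effect 2 allows. A 10-point gap already needs about 80% of the between-centre variance (0.10²/4 = 0.0025, against 0.00316).

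**A reader might infer that omitting the band makes the test conservative.** That is true of a centre-level t test. Under svy it holds only when distance explains well over a quarter of the between-centre variance; with little or no distance effect the svy test rejects too often.

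**The ranking of the two ratios is a separate matter.** In part it is, but the same sentence in the plan has to settle both.

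**Conclusion.** The concern holds in this limited form. Allocation uses the distance band; the stated analysis neither commits to it nor names one ITT risk ratio as the main result. The risk ratio is not biased, so the issue is the interval and the test.

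The size depends on an effect the Protocol does not quantify, from an interval 4-5% wider with the band (no distance effect) to one about a third narrower (distance explains everything). A centre-level model with arm and band keeps about 5% type I error across that whole range. The planned svy analysis without the band does not: its error bars can be wrong in either direction, from about 7% to about 1%.

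These figures rest on equal centres, two per arm in each band, a 40% mean rate and design effect 2. The missing commitment and the unranked ratios rest on the text alone.

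**What to change.** State in Statistical analysis, and in the repeated Statistical Plan, that the single main result is the ITT risk ratio adjusted for the distance band. Estimate it from a centre-level model with arm and band on 5 df, or from another method shown to be valid with eight clusters. Report the unadjusted ratio and the ratio further adjusted for a listed set of patient covariates as supportive. State how many centres fall in each band. Fix all this before outcome data are seen.

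Do not simply add the band to the svy model (type I error about 10%), and do not rely on declaring svy strata alone, which leaves the near-far variation in the standard error.

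The cost is one of six degrees of freedom: the 95% critical value rises from 2.447 to 2.571, about 5%. If distance has no effect, power at two-sided 0.01 falls from about 52% to about 46%. The text change is short, but it replaces svy as the basis for the main result.
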